## 4. Research methods

Design: CASAM is an open label, multinational (Spain and United Kingdom), multicenter (15 Spanish and 6 UK public institutions) observational cohort study.A SPIRIT schedule and overview of study design and data collection points can be found in Figs 1 and 2.Sample size: 150 paediatric patients on mepolizumab for SA between 6–17 years of age will be enrolled.Study Duration: Study will be conducted over 36 months (12 months pre mepolizumab initiation and 24 months after initiation). Data collection will take place until March 2026. Results will be expected in late 2025–2026.

**Fig 1 pone.0335399.g001:**
[figure not shown]
Illustrates a SPIRIT Schedule of the study.

### 4.1 Inclusion criteria

A patient will be eligible if all the following criteria apply:

Parents/guardians and/or children & adolescents aged 6–17 years at mepolizumab initiation who provides his/her written informed consent to participate prior to commencing any study related activities.Patient with a current clinical diagnosis of severe asthma (as per GINA/ ATS/ ERS/ BTS criteria) and eosinophilic phenotype (as per mepolizumab licence)Patient currently under treatment or who initiates treatment with mepolizumab at the inclusion visit based on national asthma guidelines.Patient with relevant paper or electronic-based medical records available for 12-months prior to enrolment date/index date (date of first mepolizumab injection).

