### 3.2 Secondary objective

Compare the rate of mild and moderate clinically significant exacerbations in the pre-exposure and the 12-month and 24-month post-exposure periods with mepolizumab.Compare the rate of severe asthma exacerbations requiring an ED visit in the pre-exposure and the 12-month and 24-month post-exposure periods with mepolizumab.Compare the rate of severe asthma exacerbations requiring hospitalization in the pre-exposure and the 12-month and 24-month post-exposure periods with mepolizumab.Describe changes from index date (date of mepolizumab start) in OCS dose during the post-exposure period among participants on maintenance OCS.Describe asthma related healthcare resource utilization including count of hospital admissions, ED visits, visits to HCPs, and prescription medication utilisation for asthma.Compare prescription medication utilisation (pick up) of ICS & rescue medications in the pre-exposure and the 12-month post-exposure period with mepolizumab treatment.Compare the level of asthma control at baseline and the 12- and 24-month post-exposure periods.Determine and compare the level of asthma severity measured by composite asthma severity index (CASI) score at baseline and the 12- and 24-month post-exposure periods.Determine patterns of mepolizumab usage including adherence/persistence, duration of therapy, discontinuation, and reasons for discontinuation.Determine incidence of Mepolizumab-related adverse events – parents/ patients/ physicians reported.Describe the sociodemographic, socioeconomic, and clinical characteristics (including comorbidities) of the patients under mepolizumab treatment.Describe the Health-Related Quality of Life (HRQL) of patients treated with mepolizumab at the pre-exposure and post-exposure periods.

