### 4.3 Sample size calculation

To detect a 50% decrease in exacerbation rate with 90% power at a 5% significance level during a 12-month mepolizumab treatment study for children (6–11 years old) with severe uncontrolled eosinophilic asthma, assuming a 25% participant withdrawal rate (20% in the first year and 5% in the second year) and accounting for their data contribution (4 months in the first year and 18 months in the second year), you would need around 80 participants. This is based on data from study NCT02377427 (Part B), where 30 similar patients experienced a 69% (from 3.47/year to 1.09/year) reduction in exacerbation rate while receiving mepolizumab every 4 weeks for 12 months.

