4. A set of **ad-hoc questions** to collect school absenteeism: absenteeism, late arrivals, or early departures from school in the previous, missed school-related activities, rescue inhaler utilization at school in the previous 12 months before inclusion and every 3 months in the follow-up period.
5. **Work Productivity and Activity Impairment Questionnaire General** (WPAI-GH) [35]: to be completed during the visits by the parents/legal guardians.
6. **Paediatric Asthma Quality of Life Questionnaire** (PAQLQ): It is for children between the ages of 7 and 17 years to be completed during the visits.

**Table 3 pone.0335399.t003:** Illustrates data collection overview.

Activity	Baseline visit Retrospective data (12 months prior mepolizumab initiation and since mepolizumab initiation to inclusion visit in patients already under treatment) and current data	Follow-up visits (according to usual clinical practice, up to 24 visits are expected) *If not available in all FU visits, minimum collected at the selected visits					
		All FU visits	6 m	9 m	12 m	18 m	24 m
**Informed consent**	X						
**Inclusion/exclusion criteria**	X						

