**Clinical characteristics**							
History of asthma							
• Age on asthma onset • Previous medication for asthma (up to 12 months prior inclusion)	X						
• Degree of asthma control (c-ACT)	X	X					
• Degree of asthma severity (CASI)	X				X		X
Asthma exacerbations	X	X					
Healthcare utilization: • Number of ED visits • Number of Unscheduled Outpatient visits • Number of Hospital admissions	X	X					
Details of current asthma status: • Lung function data (if available) • Peripheral blood eosinophils (if available) • FeNO: fractional nitric oxide concentration (if available)	X	X	X		X	X	X
Co-morbidities	X						X
Active/ passive tobacco smoke exposure	X	X			X		X
Treatment with mepolizumab	X	X					
Allergic condition (IgE, skin prick test or Specific IgE to aeroallergens)	X						
Concurrent medications • OCS • ICS • Rescue medication • Other asthma medication	X	X					
Satisfaction with treatment (VAS)	X (if patient already under treatment)		X		X	X	X
School and work absenteeism	X	X					
Safety assessments	X	X					
PAQLQ (Paediatric Asthma Quality of Life Questionnaire)	X				X		X

No additional study visits will be arranged, data will be collected at usual asthma healthcare visits (routine or unscheduled, remote or face to face).

**Pre-exposure period** covers the 12-month period prior to mepolizumab initiation and is retrospectively collected.

**Post-exposure period** covers up to 24 months after mepolizumab initiation and can be partly retrospective and partly prospective.

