### 4.6 Statistics

Descriptive statistical analysis will provide an overview of patient demographics and baseline characteristics. Continuous variables will be described using mean, standard deviation, median, percentiles, and range. Categorical variables will be summarized with frequencies and percentages. Significance will be determined using a p-value threshold of 0.05.

Primary analysis: Compare the 12-month post-exposure period with the pre-exposure period for each participant

Secondary analyses: Include both the 12-month and 24-month post-exposure periods

The exacerbation rate will be analysed using a Negative Binomial regression via generalised estimating equations with covariates of time (pre-, post-exposure) and country

All statistical analyses will be carried out using the statistical package SAS

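### Patients must still be on mepolizumab at inclusion, yet time counts from the first injection, so persistence is overstated by design

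*Protocol article*

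**What the plan says.** The Protocol article, section 4.1, sets treatment status at inclusion as "Patient currently under treatment or who initiates treatment with mepolizumab at the inclusion visit based on national asthma guidelines". Neither 4.1 nor 4.2 admits a patient who has already stopped, caps the time since the first dose, or limits the share of already-treated patients.

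Sections 3.2 and 4.1 set the index date at the start of mepolizumab. The text below Table 3 in section 4.4 says that the post-exposure period "covers up to 24 months after mepolizumab initiation and can be partly retrospective and partly prospective". The header of Table 3 provides for retrospective data "since mepolizumab initiation to inclusion visit in patients already under treatment".

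One secondary objective in section 3.2 is to "Determine patterns of mepolizumab usage including adherence/persistence, duration of therapy, discontinuation, and reasons for discontinuation"; another is the incidence of mepolizumab-related adverse events. The primary analysis in section 4.6 is to "Compare the 12-month post-exposure period with the pre-exposure period for each participant", with the exacerbation rate modelled by "Negative Binomial regression via generalised estimating equations with covariates of time (pre-, post-exposure) and country".

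**The concern.** Eligibility is judged at the inclusion visit, but the clock starts at the first injection. For an already-treated patient these dates differ, and the patient is in the study only because treatment lasted until the later one. This is left truncation: early stoppers are filtered out, and the stretch from initiation to inclusion is immortal time with respect to discontinuation. A patient enrolled after 24 months on drug is persistent at 24 months by construction.

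Persistence, discontinuation and duration of therapy are directly affected, because membership of the cohort depends on the outcome being measured. This needs no assumption about who benefits. It needs only that some enrolled patients were already on treatment and that some initiators stopped before they could be included.

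The same filter can reach adverse-event incidence, if events that lead to stopping are lost with the stoppers, and the exacerbation comparison, if those who stop respond worse. Both matter in a study meant to describe long-term safety and effectiveness in routine paediatric care.

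**Working it through.** **Inputs from the Protocol article, section 4.3.** The plan is "assuming a 25% participant withdrawal rate (20% in the first year and 5% in the second year"; first-year withdrawals contribute 4 months of data and second-year withdrawals 18 months.

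**Assumptions, because the documents give no figure.** Withdrawal is read as stopping treatment. The share of already-treated patients, their time on drug at entry, and the response and event risk of stoppers are illustrative.

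The plan gives no persistence figure to reproduce. Its two withdrawal rates add to the stated total (20% + 5% = 25%). Its sample size of around 80 depends on a dispersion that is not stated, and nothing below uses it.

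**Step 1: discontinuation, simplest case.** Let p be the share of the enrolled cohort that entered after more than 12 months on drug. These patients cannot have stopped in year 1, so apparent 12-month discontinuation = (1 − p) × 20%.

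- p = 25%: 0.75 × 20% = 15%
- p = 50%: 0.50 × 20% = 10%
- p = 75%: 0.25 × 20% = 5%

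**Step 2: entry spread over time.** Let early stoppers (20%) stop at 0–8 months (mean 4), second-year stoppers (5%) at 12–24 months (mean 18), and 75% stay on. If already-treated candidates are approached uniformly over 0–12 months, an early stopper is still on drug with probability 4/12 = 1/3. Over 0–24 months this is 4/24 = 1/6, and 18/24 = 0.75 for a second-year stopper.

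- 0–12 months: eligible = 0.20/3 + 0.05 + 0.75 = 0.867; early stoppers = 0.067/0.867 = 7.7%.
- 0–24 months: eligible = 0.20/6 + 0.05 × 0.75 + 0.75 = 0.821; early stoppers = 0.033/0.821 = 4.1%.

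Mixing with new starters, where f is the share of candidates already treated, gives the observed 12-month persistence below (true value 80%). For example, with f = 50% and entry over 0–12 months, early stoppers are (0.10 + 0.033)/(0.50 + 0.433) = 14.3%.

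| f | entry over 0–12 months | entry over 0–24 months |
|---|---|---|
| 25% | 82.8% | 83.4% |
| 50% | 85.7% | 87.2% |
| 75% | 88.9% | 91.3% |
| 100% | 92.3% | 95.9% |

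A simulation of 1,000,000 initiators under these assumptions agrees.

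**Step 3: primary rate ratio.** Assume a ratio of 0.45 in stayers, 1.0 in early stoppers, and equal pre-treatment rates; p is as in step 1.

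- Each patient counted equally: all initiators 0.8 × 0.45 + 0.2 × 1.0 = 0.56; cohort = p × 0.45 + (1 − p) × 0.56.
- Weighted by person-time, with stoppers giving 4 of 12 months: all initiators (9.6 × 0.45 + 0.8 × 1.0)/10.4 = 5.12/10.4 = 0.492; cohort = [p × 5.4 + (1 − p) × 5.12]/[p × 12 + (1 − p) × 10.4].

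| p | equal weight (true 0.56) | shift | person-time (true 0.492) | shift |
|---|---|---|---|---|
| 25% | 0.533 | 0.03 | 5.19/10.8 = 0.481 | 0.01 |
| 50% | 0.505 | 0.055 | 5.26/11.2 = 0.470 | 0.02 |
| 75% | 0.478 | 0.08 | 5.33/11.6 = 0.459 | 0.03 |

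If stoppers respond as stayers do, the ratio is the same in every cohort and the shift is zero.

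**Step 4: adverse events.** Assume that 10% of stayers and 50% of early stoppers have an event. The true proportion is 0.8 × 10% + 0.2 × 50% = 18%. With a share s of early stoppers, the cohort shows 10% + 40% × s. For s = 15%, 10% and 5% (step 1) this is 16%, 14% and 12%. If the two groups have equal risk, there is no bias.

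**The case against.** Admitting already-treated patients is an open and practical choice for a rare paediatric disease, and the Limitations section names enrolment bias and follow-up bias. The article fixes a model only for the exacerbation rate, so it does not commit to a naive analysis of persistence or adverse events. Delayed entry and sensitivity analyses may be in a statistical analysis plan that is not shown. The 20% is withdrawal from the study, not a discontinuation rate, and the share of already-treated patients is unknown.

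Much of this limits the size of the point. The figures are illustrations, and it would be wrong to say that the article prescribes a faulty persistence analysis. What remains is in the text: the eligibility rule and the time origin are both fixed, and together they produce the selection. The limitations give neither mechanism nor remedy, and a model with only period and country cannot separate the two kinds of patient.

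A reader might infer that every output is biased in the drug's favour, or that the primary result is seriously inflated. The documents do not support this. For exacerbations and adverse events the bias needs stoppers to differ from stayers, and nothing in the article shows that they do; some stop for reasons unrelated to response. A ratio of 1.0 in stoppers is an extreme value. The equal-weight figures also set aside the plan's own allowance that first-year withdrawals contribute only 4 months. Since section 4.6 states neither an offset nor whether time after stopping counts, both weightings are shown.

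**Conclusion.** The point holds for persistence, discontinuation and duration of therapy: pooled from the first injection, they favour the drug by design. The size depends on the unknown mix. Discontinuation of 20% could appear as 15% to 5% if a quarter to three quarters of the cohort enrolled after more than a year on drug.

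For adverse-event incidence and the exacerbation ratio the bias is conditional on early stoppers having more events or responding worse. Even with stoppers assumed to gain nothing, the primary ratio moves by about 0.01 to 0.03 by person-time, or 0.03 to 0.08 with equal weights. That is small beside the 50% decrease the study is sized to detect, so the primary comparison is not overturned. This should be fixed, mainly for the persistence and safety objectives.

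**What to change.** 1. For persistence, time to discontinuation and adverse-event incidence, set time zero at the first injection and let each patient enter the risk set at the inclusion date. Define the two dates separately, since the medical-records criterion in section 4.1 runs enrolment date and index date together.
2. Report the exacerbation rate ratio separately for new starters and already-treated patients, through a period-by-group interaction in the GEE model, with the new-starter ratio as a pre-specified sensitivity analysis beside the pooled one.

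Both are changes of analysis wording. The mepolizumab start date is listed in Table 1, and the inclusion visit is the baseline visit of Table 3, so no new data or visits are needed. The cost is precision. The new-starter interval is wider, and under delayed entry the early months rest mainly on patients enrolled near initiation. Events and time before inclusion leave the incidence estimate and can be described separately.

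Opening section 4.1 to patients who have already stopped would remove the selection at source, but it needs an amendment and new consent, and the point does not depend on it.

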### 4.2 Exclusion criteria

A participant will not be eligible if any of the following criteria apply:

Patient who does not meet the inclusion criteria.Patient who has participated in an asthma monoclonal antibodies drug interventional clinical trial in the previous 12-months to mepolizumab initiation.

### 4.3 Sample size calculation

To detect a 50% decrease in exacerbation rate with 90% power at a 5% significance level during a 12-month mepolizumab treatment study for children (6–11 years old) with severe uncontrolled eosinophilic asthma, assuming a 25% participant withdrawal rate (20% in the first year and 5% in the second year) and accounting for their data contribution (4 months in the first year and 18 months in the second year), you would need around 80 participants. This is based on data from study NCT02377427 (Part B), where 30 similar patients experienced a 69% (from 3.47/year to 1.09/year) reduction in exacerbation rate while receiving mepolizumab every 4 weeks for 12 months.

### 4.4 Data collection

Pseudonymized data will be recorded by nominated member(s) of the research team, into the eCRFs of the EDC system provided by the sponsor. Data in the EDC system are kept in a central location and all data will be transmitted to a central database. Confidentiality will be taken care of at each step. Each participant will have an eCRF and a unique identification number. Tables 1–3 illustrates details of data and patient reported variables collected and data collection process respectively.

**Table 1 pone.0335399.t001:** Illustrates baseline data collected.

1. Demographic characteristics:
◦ Age at mepolizumab initiation
◦ Gender (male/female)
◦ Weight (also collected at follow-up visits)
◦ Height (also collected at follow-up visits)
◦ BMI (auto calculated variable) (also calculated at follow-up visits)
◦ Socioeconomic situation (number of people aged 10 or older and number of people aged 1-9/number of rooms (bedrooms and living room) at baseline
**2. Clinical characteristics:**
◦ History of asthma:
▪ Age at asthma onset
▪ Degree of asthma control (c-ACT score at baseline and all follow-up visits)
▪ Degree of asthma severity (CASI score at baseline, 12- and 24 months)
▪ Previous medication for asthma during the 12 months before mepolizumab initiation: type, dose, discontinuation date and reason for discontinuation
◦ Details of current asthma status at baseline and follow-up visits
▪ Lung function data: FEV1 and FVC (if available)
▪ Peripheral blood eosinophils (if available)
▪ FeNO (if available)
◦ History of asthma exacerbations:
▪ Count exacerbations in the year before starting mepolizumab and between follow-up visits.
◦ Co-morbidities at baseline (retrospectively) and at 24 months: atopic dermatitis, allergic rhinitis, obesity, food allergies, GERD, psychological factors, breathing dysfunction (EILO, hyperventilation).
◦ Allergic condition (IgE, skin prick test or Specific IgE to aeroallergens) at baseline.
3. Tobacco smoke exposure at baseline and follow-up visits: Yes (active/ passive)/No.
4. Treatment with mepolizumab at baseline and follow-up visits: type (home/hospital), dose, dose changes, start and end date, discontinuation date and reason for discontinuation.
5. Healthcare utilisation at baseline (during the 12 months before study inclusion) and between follow-up visits.
i. Number of Emergency Department (ED) visits
ii. Number of Unscheduled Outpatient visits
iii. Number of Hospital admissions
6. Satisfaction with treatment with mepolizumab (patients/parents/HCP): VAS 0-5 (very unsatisfied to very satisfied.
7. Adverse Events related to mepolizumab reported by parents/patients/physicians
8. Adapted version of WPAI questionnaire for work productivity and absenteeism (to be completed by parents/legal guardian)
9. Days of school absenteeism (direct question to the parents/tutors)

**Table 2 pone.0335399.t002:** Illustrates overview of patient reported variables collected.

1. c-ACT (Children Asthma Control Test) [33]: It will be completed at baseline and follow-up visits.
2. **Composite asthma severity index (CASI) [****34****]**: It will be completed at baseline and follow-up visits.
3. **Visual Analog Scale (0–5) to measure satisfaction** with treatment for patients, parents, and HCP at baseline (in patients already under treatment) and follow-up visits at 6, 12, 18 and 24 months.
4. A set of **ad-hoc questions** to collect school absenteeism: absenteeism, late arrivals, or early departures from school in the previous, missed school-related activities, rescue inhaler utilization at school in the previous 12 months before inclusion and every 3 months in the follow-up period.
5. **Work Productivity and Activity Impairment Questionnaire General** (WPAI-GH) [35]: to be completed during the visits by the parents/legal guardians.
6. **Paediatric Asthma Quality of Life Questionnaire** (PAQLQ): It is for children between the ages of 7 and 17 years to be completed during the visits.

**Table 3 pone.0335399.t003:** Illustrates data collection overview.

Activity	Baseline visit Retrospective data (12 months prior mepolizumab initiation and since mepolizumab initiation to inclusion visit in patients already under treatment) and current data	Follow-up visits (according to usual clinical practice, up to 24 visits are expected) *If not available in all FU visits, minimum collected at the selected visits					
		All FU visits	6 m	9 m	12 m	18 m	24 m
**Informed consent**	X						
**Inclusion/exclusion criteria**	X						

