**Demographics/socioeconomic characteristics**							
• Age at mepolizumab initiation • Gender (male/female) • Socioeconomic situation	X						
• Weight • Height • Body Mass Index (auto calculated)	X	X			X*		X*
	**Baseline visit** Retrospective data (12 months prior inclusion) and current data	**All FU visits**	**6 m**	**9 m**	**12 m**	**18 m**	**24 m**

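### Baseline healthcare-utilisation counts are anchored at study inclusion, while the pre-exposure period is anchored at mepolizumab initiation; for children already on treatment the two windows differ

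*Protocol article*

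**What the plan says.** Several places in the protocol article anchor the baseline window at mepolizumab initiation:

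- The period definition at the end of section 4.4 says that pre-exposure "covers the 12-month period prior to mepolizumab initiation and is retrospectively collected".
- Table 1 item 2 gives the exacerbation window: "Count exacerbations in the year before starting mepolizumab and between follow-up visits".
- Table 1 item 2 also gives the medication window: "Previous medication for asthma during the 12 months before mepolizumab initiation".
- The first header of the baseline column in Table 3 reads "12 months prior mepolizumab initiation and since mepolizumab initiation to inclusion visit in patients already under treatment". It keeps the on-drug stretch before inclusion apart from the pre-drug year.

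Other places anchor it at study inclusion:

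- Table 1 item 5, for ED visits, unscheduled outpatient visits and hospital admissions: "Healthcare utilisation at baseline (during the 12 months before study inclusion) and between follow-up visits".
- The header of the same Table 3 column where it is repeated above the clinical block, which holds the exacerbation and healthcare-utilisation rows: "Retrospective data (12 months prior inclusion) and current data".
- The previous-medication row in that block, which gives a look-back of up to 12 months from inclusion. This conflicts with Table 1 item 2.

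Section 4.1 admits both children who start mepolizumab at the inclusion visit and children already receiving it. Its records criterion asks for "medical records available for 12-months prior to enrolment date/index date (date of first mepolizumab injection"), naming two dates as if they were one. The post-exposure period "covers up to 24 months after mepolizumab initiation and can be partly retrospective and partly prospective".

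**The concern.** The two anchors coincide only for children who start treatment at the inclusion visit. For a child already on mepolizumab, a 12-month window ending at inclusion contains treated months and drops the same number of months from the start of the true pre-exposure year. Because post-exposure runs from initiation and may be collected retrospectively, those treated months can also be counted as post-exposure.

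Section 4.5 follows admissions, ED visits and visits to healthcare providers over both the pre- and post-exposure periods. If mepolizumab reduces these events, treated months counted as baseline lower the before figure, and the before/after ratio moves towards 1. The size of the shift is set by who happened to be recruited, not by the drug. Table 1 lists the item 5 variables as numbers of events. If only totals are entered, the analyst cannot move events back to the right period afterwards.

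ED visits and admissions are also qualifying criteria for the primary endpoint, and exacerbations needing them are secondary endpoints. Whether the inconsistency reaches those rates depends on how they are derived, which the article does not say.

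**Working it through.** The plan gives no figure for this point, so there is none to reproduce. The check has two parts.

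**1. Which months the inclusion window covers.** Count months from the first injection as month 0. The true pre-exposure year is −12 to 0.

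- Included at month 0: window −12 to 0. Correct.
- Included at month 6: window −6 to 6. Six pre-drug months are kept, six are lost, and six treated months are added.
- Included at month 12: window 0 to 12. This is exactly the 12-month post-exposure period, with no pre-drug time.
- Included at month 18: window 6 to 18. All treated time.

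For utilisation, Table 1 item 5 and the Table 3 header over its row agree with each other on inclusion and disagree with the period definition. For exacerbations, Table 1 item 2, the period definition and the first Table 3 header say initiation, and only the repeated header says inclusion.

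**2. How far the ratio would move.**

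Inputs:
- True post/pre ratio RR = 0.50. This is borrowed from the 50% decrease in section 4.3, which concerns exacerbations; the article gives no effect size for utilisation.
- w = fraction of the 12 months before inclusion spent on drug (assumed).
- p = share of the cohort already treated at inclusion (assumed; not given).
- Event rates are taken as constant before and on drug, with the post-exposure count itself correct.

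For one child, the apparent baseline rate as a multiple of the true one is (1 − w) + w × RR, and the apparent ratio is RR divided by that.

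- 6 months on drug, w = 0.5: baseline 0.5 + 0.5 × 0.5 = 0.75; ratio 0.50 / 0.75 = 0.67.
- 12 or more months, w = 1: baseline 0.50; ratio 0.50 / 0.50 = 1.00.

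With the stronger effect in the reference study of section 4.3, RR = 1.09 / 3.47 = 0.314. Six months on drug then gives 0.314 / (0.5 + 0.5 × 0.314) = 0.48, and 12 or more months again gives 1.00.

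For the cohort, the apparent ratio is RR / [1 − p × w × (1 − RR)]. With RR = 0.50:

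| Already treated (p) | all 6 months on drug | all 12 or more months on drug |
|---|---|---|
| 25% | 0.53 | 0.57 |
| 50% | 0.57 | 0.67 |
| 75% | 0.62 | 0.80 |
| 100% | 0.67 | 1.00 |

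If time on drug among the already treated is instead spread evenly over 0 to 24 months, the mean of w is 0.5 × 0.5 + 0.5 × 1 = 0.75. The cohort ratio is then 0.55, 0.62 and 0.70 for p = 25%, 50% and 75%. With the window anchored at initiation it stays at 0.50 throughout.

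**The case against.** The strongest reply is that the design itself is right. The formal definition, the stated 12 months before and 24 months after initiation, the exacerbation count in Table 1 item 2 and the fuller Table 3 header all use initiation. Exacerbations and healthcare utilisation are separate items in Table 1 and separate rows in Table 3. The ED and hospitalisation objectives in section 3.2 concern exacerbations requiring that care, and the utilisation objective there is worded as descriptive.

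Most of this stands, and it rules out three stronger readings.

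- A reader might infer that the primary rate ratio is wrong. The documents do not support that: the primary variable has its own window, correctly anchored, and nothing says that it is built from the item 5 counts. Only the repeated Table 3 header points the other way.
- A reader might infer from the records criterion that a child 10 months on drug qualifies with 2 months of pre-drug records. The parenthesis identifies the date as that of the first injection, so this is loose wording and not an established eligibility gap.
- A reader might want the school-absence recall in Table 2, also set before inclusion, moved as well. Section 3.3 compares absenteeism at baseline, not over the pre-exposure period, and moving the recall could ask families of long-treated children about distant events that charts cannot supply.

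What the reply does not remove is item 5. Its own wording and the header over its Table 3 row both say inclusion, and section 4.5 uses those variables for both periods. A site following the tables would record treated time as baseline.

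**Conclusion.** The protocol contradicts itself on the baseline window, and the item 5 window is wrong against the protocol's own definition of pre-exposure. For children already on mepolizumab, the baseline ED, unscheduled-visit and admission counts include on-drug time and miss some or all of the pre-exposure year. If the drug works, the bias in the utilisation comparison runs towards no effect.

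Under an assumed true ratio of 0.50, the apparent ratio for an individual child is 0.67 at 6 months on drug and 1.00 at 12 months or more. The cohort figures are illustrations only, because neither the already-treated share nor time on drug is given.

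The exacerbation-based ED and hospitalisation rates, and the primary rate, are affected only if they are derived from the item 5 counts or if sites apply the repeated Table 3 header to the exacerbation row. The eCRF and the full protocol are not shown, so whether either happens is not known.

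**What to change.** - In Table 1 item 5, the repeated Table 3 header and the Table 3 previous-medication row, replace the inclusion-based look-back with the 12 months before mepolizumab initiation (index date).
- State that events between initiation and inclusion in children already under treatment belong to the post-exposure period.
- In section 4.1, remove the enrolment date from the records criterion, so that it plainly requires records for the 12 months before the index date.
- Check the baseline utilisation counts already entered for children on treatment at inclusion. Where the window ran to inclusion, re-abstract from the charts.

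The cost is a wording change, site queries and some chart re-abstraction, with no extra visits. Section 4 has data collection running until March 2026. The correction is best made at data capture, since a wrongly windowed total may not be recoverable at analysis.
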